### Data collection and patients follow-up

All patients will be reviewed at the standard six weeks and 12 months outpatient clinic visits after treatment. Standardized patient-reported outcome questionnaires will be collected during the outpatient visit, by performing telephone interviews or using a secure online questionnaire platform: Castor Electronic Data Capture (EDC) system. Electronic medical records will be reviewed to collect baseline characteristics regarding history of previous injuries of the affected shoulder, age, sex, BMI, ASA sore, trauma date, trauma mechanism, time from injury to treatment, current profession, and physical demands. Data collection will be performed by reviewing electronic medical records, operative reports, radiology reports and patient interviews by independent research fellows. All data will be stored in a research folder that can only be accessed by the principal investigator and independent research fellows. Data will be pseudonymized and a file to decode these data will be stored in a research folder only accessible by the principal investigator and independent research fellows.

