## Abstract

**Background:**

The proximal humerus fracture is a common injury, but the optimal management is much debated. The decision for operative or nonoperative treatment is strongly influenced by patient specific factors, regional and cultural differences and the preference of the patient and treating surgeon. The aim of this study is to compare operative and nonoperative treatment of proximal humerus fractures for those patients for whom there is disagreement about optimal management.

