## Introduction

The proximal humerus fracture is a common injury, accounting for 5.7% of all fractures and the third most common fracture type in the elderly population [1,2]. The optimal management of acute proximal humerus fractures, i.e. operative or nonoperative treatment, is much debated [3–5]. Several meta-analyses have been inconclusive whether operative treatment of proximal humerus fractures is superior to nonoperative treatment [3–5].

The Proximal Fracture of the Humerus Evaluation by Randomization (PROFHER) study, a multicenter randomized controlled trial including 250 patients, is to date the largest study that compared outcomes following operative and nonoperative treatment of proximal humerus fractures. The PROFHER trial evaluated the Oxford Shoulder Score, the Short-Form 12, complications, subsequent therapies, and mortality. The study found no statistically significant or clinically relevant differences in outcomes between the operative and nonoperative treatment groups [6]. However, the validity and generalizability of these findings have been called into question [7,8]. The inclusion of patients in the PROFHER trial was not consecutive. In total, 1250 patients were screened, of which 563 patients were found eligible for inclusion. However, only 250 patients eventually consented to take part in the study. Furthermore, the 109 patients who received operative treatment were treated by 66 different surgeons in 30 different hospitals. The low number of cases per surgeon could have influenced the results of this study. What is more, since the inclusion rate is so low, generalizing results from such a selective group is not straightforward [9].

In practice, patient-specific factors can have a large impact on the decision for operative or nonoperative management, which leads to challenges during surgical trials. Furthermore, both patients and surgeons can have a strong preference for a certain treatment, which forms an obstacle for randomization in surgical trials [10]. The patient populations encountered in daily clinical practice often differ from the highly selected patient populations enrolled in randomized controlled trials [11].

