### Intervention

The decision for operative or nonoperative treatment is left to the treating orthopedic trauma surgeon at the participating hospitals. The actual treatment will be initiated prior to inclusion in the LADON study.

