### Expert panel progress

After informed consent, pseudonymized data sets including radiographs, AO fracture classification, and baseline patient characteristics during first presentation will be collected. The individual patient data sets will be made available on a secure online platform. All relevant data to reach a “clinical” decision will be made available, including basic clinical information, radiographs, key images of CT-scans if available and radiology reports. The data will be presented to an expert panel of each country, blinded to the already initiated treatment. The expert panels will consist of an equal distribution of representatives from both countries, three orthopedic trauma surgeons from the participating Dutch centers and three orthopedic trauma surgeons from participating Swiss centers. Members of each panel will independently decide on the preferred management, operative or nonoperative treatment, for each individual case. Patients can be included in the study if the majority of experts in one country, i.e., minimally two out of three, disagree with the received treatment in the other country. For example, patients are eligible if they would have received operative treatment based on the expert opinions in e.g. Switzerland, while in fact they received nonoperative treatment in the Netherlands, and vice versa. Patients will be excluded when the majority of the panel in one country agree on the received treatment in the other country. This will lead to a group of patients for whom there is disagreement on the optimal management, operative or nonoperative treatment. Both operative and nonoperative treated patients will be send to the expert panels to ensure blinding. A flow chart of the patient recruitment is shown in Fig 1. For practical efficiency we chose to perform the expert panel evaluation prior to inclusion rather than include all eligible patients and perform an expert panel evaluation afterwards.

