### Statistical analysis

Descriptive results will be presented as mean values with standard deviations and range (SD, range), median values with interquartile range (IQR) or absolute numbers and percentages (%). To control for potential confounding, we will conduct propensity score matching. The propensity score will be estimated using binary logistic regression analysis, with operative or nonoperative treatment as the dependent variable and age, sex, BMI, ASA score, AO classification as covariates in the model. The primary analysis will be performed within the dataset of propensity score matched patients. Normal distribution will be confirmed using the Shapiro–Wilk test. Correlation between continuous variables will be measured using the Pearson correlation coefficient. Missing data will not be imputed. Differences between study groups will be analysed using the independent sample t-test, Mann–Whitney U test, or the Chi-square test. A two-tailed p-value less than 0.05 will be considered significant.

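### Patient preference is named as a driver of treatment but is absent from the listed data, and the inclusion rule can admit patients on whom both expert panels agree

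*Protocol article*

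**What the plan says.** The abstract's Background describes the choice between operative and nonoperative treatment as "strongly influenced by patient specific factors, regional and cultural differences and the preference of the patient and treating surgeon". The Introduction adds, as an obstacle to randomised surgical trials, that "both patients and surgeons can have a strong preference for a certain treatment".

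Under Intervention, "The decision for operative or nonoperative treatment is left to the treating orthopedic trauma surgeon at the participating hospitals", and "The actual treatment will be initiated prior to inclusion in the LADON study".

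Under Expert panel progress, each case goes to three Dutch and three Swiss surgeons, blinded to treatment, who vote independently. They see the data relevant to a clinical decision, "including basic clinical information, radiographs, key images of CT-scans if available and radiology reports". A patient qualifies if a majority in one country, "minimally two out of three, disagree with the received treatment in the other country".

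Under Data collection and patients follow-up, the baseline items are "history of previous injuries of the affected shoulder, age, sex, BMI, ASA sore, trauma date, trauma mechanism, time from injury to treatment", then current profession and physical demands. Under Statistical analysis, the propensity model takes "age, sex, BMI, ASA score, AO classification as covariates in the model".

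The abstract describes the study population as patients on whom the experts disagree. The abstract and the Discussion both call that disagreement proven, and say the selection makes the two groups comparable and mitigates confounding. The primary outcome is the patient-reported QuickDASH at 12 months.

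**The concern.** The design takes its contrast from differences in national practice, applied to patients in the middle of a continuum where experts differ. That works only if an included patient's treatment reflects local practice and not something about the patient that also bears on the outcome.

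Patient preference is a factor of that kind, and the plan itself names it. A patient who declines or asks for surgery may differ in expectations, activity or the way disability is rated, and knows which treatment was given. Matching on age, sex, BMI, ASA score and AO class would not remove such a difference. Because the rule is keyed to treatment received, it can also admit patients who lie outside the zone of expert disagreement. At stake are the comparability of the arms and the description of whom the result applies to.

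**Working it through.** **1. The rule against the stated population.** Take the two routes seen so far: Dutch patients treated nonoperatively and Swiss patients treated operatively.

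| Country, treatment received | Dutch majority | Swiss majority | Panels differ? | Included? |
|---|---|---|---|---|
| NL, nonoperative | nonoperative | operative | yes | yes |
| NL, nonoperative | operative | operative | **no** | **yes** |
| NL, nonoperative | nonoperative | nonoperative | no | no |
| CH, operative | nonoperative | operative | yes | yes |
| CH, operative | nonoperative | nonoperative | **no** | **yes** |
| CH, operative | operative | operative | no | no |

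The bold rows satisfy the rule although the panels agree, possibly all six experts. A Dutch patient who declined advised surgery, or a Swiss patient who asked for surgery against advice, can land there. So can a patient whose surgeon simply departed from the home panel's view. The home panel's vote is cast but not used.

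**2. Where preference could be picked up.** It is not in the listed baseline items, not among the data named for the panels, and not among the five propensity covariates.

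**3. What Trial status adds.** All 102 Dutch inclusions were nonoperative and all 80 Swiss inclusions operative. Nobody has entered on treatment against the national pattern. Preference in the same direction as local practice (Dutch refusal, Swiss request) is not excluded.

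**4. The plan's own sample size.** Difference 8, SD 14, two-sided alpha 0.05, power 80%: the t-based solution is 49.05 per arm, so 50, which reproduces the stated figure. With 220 recruited and losses of 20% and 40%, 220 × 0.8 × 0.6 = 105.6, or about 53 per arm.

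**5. Illustration of size (assumptions, not document figures).** Let q be the share of preference-led treatments, and suppose 95% of these contradict the other panel. Let r be the proportion of surgeon-led cases that contradict it. The share of preference-led patients in an included arm is

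q × 0.95 / [q × 0.95 + (1 − q) × r].

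Feasibility gives up to 40% operative in Switzerland and up to 90% conservative in the Netherlands. If these are taken at face value and the two practices are nested on one continuum, r = 30/40 = 0.75 for Swiss operations and r = 30/90 = 1/3 for Dutch nonoperative cases. A value of 0.50 widens the operative range.

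| q | Operative, r = 0.75 | Operative, r = 0.50 | Nonoperative, r = 1/3 |
|---|---|---|---|
| 3% | 3.8% | 5.6% | 8.1% |
| 5% | 6.3% | 9.1% | 13.0% |
| 10% | 12.3% | 17.4% | 24.1% |

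If these patients differ by an assumed 8 QuickDASH points, the shift in an arm mean is share × 8.

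- Opposite signs in the two arms: from 8 × (0.081 + 0.038) = 0.95 to 8 × (0.241 + 0.174) = 3.3 points.
- Same sign in both arms: from 8 × (0.081 − 0.056) = 0.2 to 8 × (0.241 − 0.123) = 0.9 points.

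Plausibility check: if 90% are treated conservatively and q = 10% of those refused surgery, refusers are 9 per 100 patients against 10 operated. Then 9/19 = 47% of those advised surgery would have declined, which looks too high. The upper end is therefore doubtful. The check is approximate, because the 90% refers to all fractures around the shoulder.

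**6. Power of a restricted analysis.** Losing 24% of one arm and the matched partners leaves 53 × 0.76 ≈ 40 per arm. Two-sample t-test power (difference 8, SD 14) is 83% at 53, 79% at 48 and 71% at 40.

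**The case against.** The article condenses a fuller protocol. It names patient interviews as a data source, and the panel data are introduced by an open list. A reader might infer that preference is never recorded; the text does not establish that, only that the lists shown omit it. Profession and physical demands are collected and are partial measures of activity, although they are not in the propensity model and do not identify a refusal or a request.

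The Introduction speaks of preference as an obstacle to randomisation, so only the abstract says directly that it drives the treatment decision. The authors also concede that not everything can be measured, and in the methods claim mitigation only to a large extent. With treatment so far coinciding with country, national practice is probably the larger driver.

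A reader might also infer a bias of 1 to 3 points. That needs assumed shares, an assumed 8-point difference and opposite signs in the two arms, none of which the document supplies. With equal signs the same inputs net to 0.2 to 0.9 points.

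These objections stand as limits on how strongly the point may be put. They do not touch the inclusion rule, which is stated in full and does admit patients on whom the panels agree, nor the five covariates, which are fixed.

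**Conclusion.** The point holds in a limited form. As written, the inclusion rule does not guarantee the population the article describes, because agreement between the panels does not exclude a patient whose treatment departed from both. Preference, which the abstract calls a strong influence, appears in neither the listed baseline data nor the propensity model. The result is a credible risk of unmeasured confounding of a self-rated outcome, not a demonstrated bias. Its size and direction cannot be derived from the document, and the illustrative figures should not be quoted as an estimate. The change is worth making because it is cheap and uses votes already held.

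**What to change.** 1. Prespecify a sensitivity analysis of the primary matched comparison restricted to patients in whom the Dutch and Swiss panel majorities differ. Both panels already vote on every case, so no new data are needed. This restores the stated population. It does not detect preference among patients on whom the panels do differ, which is why the second step is needed.

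2. If the full form does not already hold them, add two items from records or interview: the treating surgeon's recommendation, and whether the patient requested or declined treatment against it. Repeat the matched comparison in patients treated as recommended. A recorded recommendation may already reflect the patient's wishes, so this is a partial check.

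3. Report both results beside the primary one. If they differ materially from it, limit the claim that the selection mitigates confounding. Do not make agreement between estimates a formal condition for the conclusion; it would need a margin that nobody has defined.

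Cost: two form items and two further runs of the same analysis, with no change to treatment or recruitment. The items will be incomplete for the 182 patients already included (102 + 80), and the restricted sets are smaller: about 71% power if some 40 per arm remain, at SD 14 and a difference of 8.

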### Sample size considerations

As indicated above, the primary outcomes are defined as the difference in patient-reported functional outcome as measured by the QuickDASH, measured at 12 months after the injury. The developers of the QuickDASH report that a difference of eight points represents a clinically relevant difference for discriminating between improved and stable patients [22]. A previous observational cohort study by Frima et a.l [23], performed by our research group, found patients who had MIPO surgery had a QuickDASH standard deviation (SD) of 14. Sample size calculations indicate that a study with a power of 80% and two-sided statistical significance level (alpha) of 0.05 would require 2 x 50 participants. Accounting for 20% loss to follow-up and an additional 40% loss after propensity score matching (used to account for confounding, see Statistical Analysis), the total sample size is 220 participants.

#### Feasibility

The planned recruitment period to reach the required sample size is based on retrospective data on proximal humerus fractures in the participating centers. The study started simultaneously in the participating centers on July 1^st^ 2020. To reach the required sample size the recruitment period will be 24 months and an additional 12 months will be needed to collect follow-up data on all patients (Fig 3). Based on observational data from the participating hospitals, approximately 550 patients with acute displaced proximal humerus fractures are treated each year in both the Netherlands and Switzerland. In the Netherlands up to 90% of the patients with fractures around the shoulder are treated conservatively and in Switzerland up to 40% are treated operatively [15,16]. We performed a preliminary expert panel evaluation, which resulted in an overall disagreement rate of approximately 40%. The proposed recruitment period of 24 months would, after accounting for a 40% disagreement rate and loss of ineligible patients, result in 220 patients for analysis.

**Fig 3 pone.0264477.g003:**
[figure not shown]
Timeline LADON study.

### Statistical analysis

Descriptive results will be presented as mean values with standard deviations and range (SD, range), median values with interquartile range (IQR) or absolute numbers and percentages (%). To control for potential confounding, we will conduct propensity score matching. The propensity score will be estimated using binary logistic regression analysis, with operative or nonoperative treatment as the dependent variable and age, sex, BMI, ASA score, AO classification as covariates in the model. The primary analysis will be performed within the dataset of propensity score matched patients. Normal distribution will be confirmed using the Shapiro–Wilk test. Correlation between continuous variables will be measured using the Pearson correlation coefficient. Missing data will not be imputed. Differences between study groups will be analysed using the independent sample t-test, Mann–Whitney U test, or the Chi-square test. A two-tailed p-value less than 0.05 will be considered significant.

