**Fig 1 pone.0264477.g001:**
[figure not shown]
Flow chart of the patient recruitment.

In an ideal observational study all patient characteristics are measured and adjusted for. Instead of this utopia we try to identify patient subgroups for whom their profile is likely similar. We assume the patient profile is a continuum, such that on one end of the continuum all patients will receive conservative treatment, whereas on the other end of the continuum all patients will receive operative treatment. However, different hospitals (or countries) may have different preference for operative or conservative treatment, which provides a contrast that forms the basis for an observational study of these treatments. By zooming in on a patient with a similar profile, confounding by patient characteristics will, to a large extent, be mitigated. One way of identifying patients with a similar profile is to identify those patients for whom experts disagree about the appropriate treatment. The more we zoom in, the better we adjust for confounding, however, the less precise estimates will be due to fewer patients being included in the study (Fig 2).

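### The propensity model is closed at five covariates and leaves out four collected baseline variables that may confound the primary comparison

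*Protocol article*

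**What the plan says.** The Statistical analysis section gives a definite propensity model: binary logistic regression "with operative or nonoperative treatment as the dependent variable and age, sex, BMI, ASA score, AO classification as covariates in the model". It continues: "The primary analysis will be performed within the dataset of propensity score matched patients". Groups are then compared by independent t-test, Mann–Whitney U test or Chi-square test, with no covariate adjustment.

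The section on data collection and follow-up lists further baseline characteristics: "history of previous injuries of the affected shoulder, age, sex, BMI, ASA sore, trauma date, trauma mechanism, time from injury to treatment", followed by "current profession, and physical demands". No reason is given for leaving these out of the model.

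The text below Fig 1 describes the other safeguard, restriction by expert panel: "One way of identifying patients with a similar profile is to identify those patients for whom experts disagree about the appropriate treatment". It claims that this mitigates confounding to a large extent, not that it removes it. The same paragraph describes measurement of and adjustment for all patient characteristics as the ideal.

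**The concern.** Matching on the propensity score is the only statistical adjustment before the primary test, so a variable left out of that model is not picked up later. Previous injury of the same shoulder, the mechanism of the trauma, occupation and physical demands can each influence whether a surgeon operates. They can also influence an upper-limb disability score a year later. They are measured before treatment and will already be in the database.

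The Trial status section makes this sharper. The 102 Dutch patients included so far are all nonoperative and the 80 Swiss patients are all operative. Any difference between the two national populations in these variables is therefore a difference between the treatment arms. What is at stake is avoidable residual confounding in the primary QuickDASH difference.

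**Working it through.** **Inputs from the protocol article.** Difference of 8 points, SD 14, power 80%, two-sided alpha 0.05, 2 x 50 patients, losses of 20% (follow-up) and 40% (matching), total 220 (Sample size considerations). Inclusion of 102 Dutch and 80 Swiss patients (Trial status).

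**Assumed, because the documents give no figure.** The effect g of one omitted binary factor on QuickDASH, given the matched covariates, is 4 to 12 points. Its residual prevalence difference d between matched arms is 0.10 to 0.40.

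1. *The plan's own figure.* n per arm = 2 × (1.96 + 0.84)² × 14² / 8² ≈ 48.1, rounded up to 49. The t-test solution is 49.05, so 50. The stated 2 x 50 reproduces. Inflation gives 100 / (0.80 × 0.60) = 208.3, so 209. The stated 220 is slightly above this, on the safe side. Nothing below depends on that gap.

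2. *Collected against modelled.* Age, sex, BMI and ASA score are on both lists, and AO classification is collected for the expert panel. Previous shoulder injury, trauma mechanism, profession and physical demands are collected but not modelled. Time from injury to treatment is also unmodelled, but it depends partly on the treatment chosen and is rightly absent.

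3. *Possible size.* Bias = g × d. SE = 14 × √(2/50) = 2.80. Type I error = 1 − Φ(1.96 − bias/SE) + Φ(−1.96 − bias/SE). Power when the bias opposes a true 8-point effect = Φ((8 − bias)/SE − 1.96), which is 0.815 with no bias.

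| g (points) | d | Bias (points) | Share of 8 points | Type I error | Power if opposed |
|---|---|---|---|---|---|
| 4 | 0.10 | 0.4 | 5% | 0.052 | 0.775 |
| 8 | 0.20 | 1.6 | 20% | 0.088 | 0.628 |
| 12 | 0.40 | 4.8 | 60% | 0.403 | 0.207 |

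4. *Room in the model.* At the current split, the smaller arm of 220 patients would hold 220 × 80/182 = 96.7, about 97. That is 97/5 = 19.4 patients per parameter now, 97/9 = 10.8 with four more parameters, and 97/12 = 8.1 with seven more. These counts give ASA score and AO classification one parameter each, and multi-level coding would use more.

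5. *Expert votes as covariates.* With treatment following country as it has so far, a Dutch nonoperative patient enters only with at least 2 of 3 Swiss votes for surgery. A Swiss operative patient enters only with at most 1 of 3 Dutch votes for surgery. Hence every included patient with 2 or 3 Dutch votes for surgery is nonoperative, and every included patient with 0 or 1 Swiss votes for surgery is operative. The inclusion rule makes the counts partly determine treatment, so a logistic model containing them would be partly separated.

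6. *A fixed balance limit.* With 50 per arm the SE of a standardized difference is about √(2/50) = 0.20. Even under randomization, the chance that one covariate falls within ±0.1 is P(|Z| < 0.1/0.20) = P(|Z| < 0.5) ≈ 0.38.

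**The case against.** The strongest reply is that the design rests mainly on restriction, with matching only added to it. The Discussion says so in terms. Inclusion requires disagreement, and the exclusion criteria remove re-fractures, dislocations and associated ipsilateral fractures, which narrows the spread of patients further. This stands to the extent that a reader should not infer that the whole causal claim hangs on the five-covariate model. It does not remove the point. The article claims mitigation rather than removal, and adds matching for what is left.

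A second reply is that the size of the bias is assumed. This is correct. The formula concerns only the imbalance left after matching. Profession and physical demands may track age, and mechanism may track AO type, so part of any imbalance could already be matched away. The direction is unknown too. The text supports *may bias*, not a statement that the primary estimate is biased by a given amount.

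A third reply is that a separate analysis plan may exist. Balance diagnostics and coding can properly be left to it. The covariate list cannot be excused in this way, because the article states it as a closed choice.

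A reader might also infer that the vote counts are the study's own scale of patient profile and belong in the model. The article says only that disagreement is one way to find similar patients, and step 5 shows why the counts would be unsound covariates.

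**Conclusion.** The point holds in a limited form. Four collected pre-treatment variables that plausibly affect both treatment choice and outcome are left out of the only adjustment step, without a stated reason. This may bias the primary difference beyond what restriction removes.

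The size cannot be derived from the documents. The middle case in step 3 gives 1.6 points, a fifth of the 8-point target, with a type I error of about 0.09 instead of 0.05. The range of 0.4 to 4.8 points reflects the assumptions on effect and imbalance alone. Several omitted factors could add up or cancel.

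A reader might infer that a fuller model would make the arms comparable. It would not: while treatment coincides with country, differences between the countries in care, rehabilitation or reporting remain in the comparison whatever patient covariates are added.

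**What to change.** - Add previous injury of the affected shoulder, trauma mechanism, and profession or physical demands to the propensity model, or to a regression in the matched set. Code them sparsely, with about 3 to 4 extra parameters in total.
- Report standardized differences for all collected baseline variables after matching, without a hard 0.1 limit, which step 6 shows to be unrealistic at 50 per arm.
- Do not enter time from injury to treatment, and do not enter vote counts as propensity covariates. Use the vote pattern at most in a sensitivity analysis.
- State that the extended model does not address confounding by country.

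The change takes a sentence or two in the Statistical analysis section and no new data collection. It costs a few parameters and possibly more unmatched patients. Since missing data will not be imputed, gaps in the added variables may also remove patients. The assumed 40% matching loss should therefore be rechecked against the 2 x 50 target.

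### The primary test on the matched set ignores the covariates and the matching, which makes it inefficient and its error bars somewhat too wide, though not underpowered

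*Protocol article*

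**What the plan says.** The Statistical analysis section estimates a propensity score by logistic regression of treatment on age, sex, BMI, ASA score and AO classification. It then fixes the analysis set: "The primary analysis will be performed within the dataset of propensity score matched patients". For the comparison it says "Differences between study groups will be analysed using the independent sample t-test", with the Mann–Whitney U and Chi-square tests as the other options. It states no outcome model, no paired test and no variance that reflects the matching.

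The Sample size considerations section takes the position that "a difference of eight points represents a clinically relevant difference", uses an SD of 14 from earlier surgical patients, and finds that the study "would require 2 x 50 participants". The inflation to 220 in total is explained as "Accounting for 20% loss to follow-up and an additional 40% loss after propensity score matching".

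**The concern.** Matching makes the two groups alike on variables that probably also predict QuickDASH. The difference in means then varies less from sample to sample than the independent-samples formula assumes, so that formula reports a standard error that is too large. The five covariates are collected for every patient, yet they are not used where they could sharpen the estimate or correct chance imbalance left after matching on a single score.

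The plan also expects to set aside 40% of patients who have been panel-screened, have consented and have been followed. At stake are the width of the confidence interval around the treatment difference and the power to detect 8 points.

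**Working it through.** **Inputs from the article:** difference 8, SD 14, "power of 80% and two-sided statistical significance level (alpha) of 0.05", 2 × 50 evaluable, 20% loss to follow-up, a further 40% loss through matching, total 220. **Assumed, because the article gives no figure:** covariate R² of 0.1 to 0.3, equal arms, 1:1 caliper matching, and the effective sample under weighting.

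**1. The plan's own figure.** n per arm = 2 × (1.960 + 0.842)² × (14/8)² = 48.1, so 49. The t-based solution is 49.05, so 50. Power at 50 per arm is 80.8%. The stated 2 × 50 is reproduced. The inflation gives 100 / 0.8 / 0.6 = 208, so 220 is slightly generous.

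**2. What the plan delivers.** 220 × 0.8 = 176 followed; 176 × 0.6 = 105.6 matched, about 53 per arm. SE = 14 × √(2/53) = 2.72; 95% CI half-width = 1.983 × 2.72 = 5.4 points; power 83% (t-based). The target is met.

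**3. How wrong the error bars can be.** If matching balanced the covariates perfectly, the true SE would be √(1 − R²) times the reported one.

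| R² | Largest SE excess, 1/√(1 − R²) − 1 | Type I error at that limit |
|---|---|---|
| 0.1 | 5% | 3.9% |
| 0.3 | 20% | 1.9% |

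These are limits, because matching on a scalar score does not balance every covariate perfectly. Simulations of the plan used 176 followed patients and five covariates, with 54–64% retained. At R² = 0.3, the SE was 7–19% too wide across the scenarios. If k is the ratio of reported to true SE, the type I error is 2 × [1 − Φ(1.96k)]: 3.6% at k = 1.07 and 2.0% at k = 1.19, so about 2–4%. At R² = 0.1 the independent test was close to correct, within simulation noise.

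Within-pair correlation is only part of the mechanism. At R² = 0.3 it was between about 0 and 0.17 in the simulations. A correlation of 0.17 alone would give 1/√0.83 − 1 = 10%. The rest reflects balance of the groups as a whole, so putting the covariates in the model matters more than pairing alone.

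**4. Using all followed patients.** When matching keeps 54–62%, the effective sample under overlap weights was about 73–81% of 176. Taking 80% gives 141, about 70 per arm.

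| Analysis | Per arm | SE | 95% CI half-width | Power at 8 points |
|---|---|---|---|---|
| Matched set | 53 | 2.72 | 5.4 | 83% |
| Overlap weights, 80% effective | 70 | 2.37 | 4.7 | 92% |
| Overlap weights, 73% effective | 64 | 2.48 | 4.9 | 89% |

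The 73% row goes with matching that keeps about 54%, so it is not the counterpart of 53 per arm. These figures precede any gain from covariate adjustment. At 80%, the SE is 1 − 2.37/2.72 = 13% smaller. In simulation, overlap weighting with covariate adjustment had a true SE 12–18% smaller than the matched estimate.

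**5. Residual imbalance.** With 54–64% retained, the average bias of the matched estimate was under 0.2 points in every setting. Imbalance left after matching is therefore mainly a source of noise here, not of systematic error on the measured covariates.

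**The case against.** - **The loss was planned for.** The 40% is an allowance built into the 220, and power stays above 80%. This stands. A reader might infer that the study is underpowered or that patients are discarded needlessly, but the article supports neither. Matching removes patients without a comparator, and the Discussion offers it as a safeguard on top of panel selection. If the panel has already made patients alike, the real loss may be below 40%.
- **The error is conservative.** A reader might infer a false-positive risk. There is none from this source: the interval is too wide and the type I error is below 5%.
- **The size is easily overstated.** It is tempting to set pair correlation equal to R², which gives 5–20% and 3.9–1.9% across R² of 0.1 to 0.3. That holds only if pairs agree on every prognostic covariate, which matching on a scalar score does not ensure. It is equally tempting to assume a 100% effective sample under weighting, which would need a constant propensity score and does not fit a 40% matching loss.
- **The article is condensed.** The matching ratio, caliper and balance checks may be given elsewhere, and the sentence on tests covers all outcomes. That is fair for those details. The analysis set and the type of test are, however, stated, and the stated test is not the efficient one.
- **Country.** Trial status reports 102 Dutch patients, all nonoperative, and 80 Swiss patients, all operative. A narrower interval does not separate treatment from country. This stands, and applies equally to the present plan.

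**Conclusion.** The point holds as one of efficiency and conservative inference. The stated primary comparison leaves five collected covariates out of the outcome analysis and uses a standard error that ignores the balance created by matching. The excess width is roughly 7–19% if the covariates explain 30% of outcome variance, and little or none at 10%. Using all followed patients could narrow the half-width from about 5.4 to about 4.7 points and raise power from about 83% to about 92%, if matching keeps about 60% and the effective sample is about 80%. R², effective sample and equal arms are assumptions; SD 14 and the 8-point difference are the plan's own. Matching or weighting as the primary analysis is partly a choice of target population. Replacing the unadjusted test is not such a trade-off and should be done in either case.

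**What to change.** **Primary analysis in the matched set.** Replace the independent t-test for 12-month QuickDASH with a linear model of outcome on treatment plus age, sex, BMI, ASA score and AO classification, with standard errors clustered on matched pair. Report the adjusted difference with its 95% CI.

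**All followed patients.** Add overlap weighting with the same covariates in the outcome model and robust standard errors. Pre-specify it as a sensitivity analysis. If the sponsor accepts the overlap population as the target, which suits a question about patients for whom experts disagree, make it primary and keep matching as the sensitivity analysis.

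**Cost.** A change of wording, slightly more analysis work and an explicit statement of the target population. No further patients or data are needed. The report should say that neither analysis removes the confounding of treatment with country.
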